## Abstract

Acne is a multifactorial dermatosis, which is influenced not only by hormones but also by the biochemical relationship between them and the pilosebaceous unit. Inflammatory cytokines, chemokines, active oxygen, and zinc are known to be associated with the development of acne. Further, steroid metabolism is known as one of the important factors related to sebum secretion and comedone formation in acne. However, there is a lack of studies comparing these human biomarkers between healthy individuals and patients with acne. In particular, no study has investigated the relationship between human biomarkers and patterns of acne yet.

The purpose of this study is to investigate diagnostic human biomarkers in acne by comparing the biological and metabolic biomarkers between healthy individuals and patients with acne and identify the relationship between human biomarkers and patterns of acne.

This study is a protocol for a cross-sectional study. Forty healthy participants and 60 patients with acne will be recruited at 1 center. We will collect their blood samples and analyze the molecular biological and metabolic biomarkers (cytokines, chemokines, reactive oxygen species, corticotropin-releasing hormone, zinc, amino acid, 1-carbon metabolite, lipid metabolite, etc.). Further, we will administer questionnaires regarding their diet, sleep, stress, and other factors relating to acne and measure their skin elasticity.

The study protocol was approved by the Institutional Review Board of Oriental Medical Hospital at Kyung Hee Medical Center (KOMCIRB-161118-HR-062). Written informed consent will be obtained from all the participants. The trial was registered in the Clinical Research Information Service, Republic of Korea: KCT0002212.

This trial will provide evidence regarding diagnostic human biomarkers in acne and the relationship between the human biomarkers and patterns of acne.

## Introduction

1

Acne vulgaris is a common chronic inflammatory dermatosis that manifests as papules, pustules, nodules, and cysts in the pilosebaceous units on the face, chest, and back.^[1,2]^ It is one of the most common diseases during adolescence, affecting more than 85% of adolescents.^[3]^ However, according to lifestyle factors, such as diet, occupation, and stress, the incidence of adult female acne, which starts after 25 years of age, is increasing.^[4]^ Acne is caused by multiple factors, such as increased sebum overproduction, abnormal cornification of the sebaceous follicular duct, colonization of the intrafollicular duct by *Propionibacterium acnes*, and inflammation.^[5,6]^ Genetic predispositions, hormonal abnormalities, immunological disorders, and psychological, environmental, and even iatrogenic factors may contribute to the formation of acne.^[7]^ Acne remains a rare disease in non-Westernized societies; however, the adoption of Western lifestyles increases the incidence of acne. Recent studies have reported that the Western diet is over-stimulated with the mammalian target of rapamycin complex-1 (mTORC1) signaling exaggerated cell growth and proliferation and mTORC1-mediated insulin resistance due to increased milk/dairy protein consumption with high glycemic loads and abundant amounts of branched chain amino acids,^[8,9]^ increased nutrient-sensitive kinase mTORC1 activity, and decreased nuclear levels of forkhead box class O1 transcription factor, which might aggravate or promote acne development.^[2,8]^

Although Western diet,^[10]^ stress,^[11]^ and smoking^[12]^ are factors that worsen acne, the exact etiology is still unknown. There is a lack of studies comparing these human biomarkers between healthy individuals and patients with acne, and no study has investigated the relationship between human biomarkers and patterns of acne yet.

The objective of this research is to determine the diagnostic specific human biomarkers in acne by comparing the molecular biological and metabolomics biomarkers between healthy control subjects and patients with acne, identify the relationship between human biomarkers and patterns of acne, and explore the correlation between biomarkers and various lifestyle factors affecting acne.

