### Aim of the study

2.1

The objective of this study is to discover novel specific biomarkers associated with the pathogenesis of acne by analyzing metabolomics/molecular biomarkers and skin biophysical parameters between healthy individuals and patients with acne, to compare the differences in these biomarkers according to the severity of acne, and to explore the correlation between such biomarkers and various factors, such as acne symptoms, dietary habit, stress level, sleep pattern, and menstrual pattern.

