### Statistical methods

2.8

Data will be displayed as means ± standard deviations for continuous data or n (%) for categorical data. Statistical analyses will be conducted with a 95% confidence interval using the SPSS 21.0 (IBM SPSS Statistics, New York, NY). An independent *t* test will be performed for the comparison of specific biomarkers associated with the pathogenesis of acne by analyzing metabolomics/molecular biomarkers and skin biophysical parameters between the healthy subjects and participants with acne vulgaris. One-way analysis of variance will be performed for the comparison of the differences in these biomarkers among 3 groups (mild, Gr 1-2; moderate, Gr 3-4; severe, Gr 5-6), which we will classify in accordance with the severity of acne using the KAGS. The correlation between the biomarkers and various factors, such as acne symptoms, dietary habit, stress level, sleep pattern, and menstrual pattern, will be examined using the Pearson correlation test. The mean value of a variable will be used in place of the missing data value for that same variable.

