## Discussion

3

Although accumulating evidence underlines the role of Western diet, stress, and smoking in the pathogenesis of acne, the pathogenesis and aggravating factors of acne are not yet fully elucidated. Therefore, the metabolomics/molecular biomarkers could be an issue when discussing acne management with patients.

This will be the first protocol that would discover new diagnostic biomarkers in acne by analyzing metabolomics/molecular biomarkers and skin biophysical parameters between healthy individuals and patients with acne, compare the differences in these biomarkers according to the severity of acne, and explore the correlation between these biomarkers and various factors. In this study, we will analyze the molecular biomarkers, including zinc, calcium, and ROS, as well as existing known inflammatory cytokines and chemokines, and targeted and untargeted metabolite biomarkers, such as steroidal hormones, fatty acids, and endogenous small metabolites closely related to energy metabolism and lipid/steroid biosynthesis in terms of systems biology. We will also use the skin biophysical measurement devices Sebumeter SM815, Skin-Thermometer ST500, and Reviscometer RVM600 and questionnaires that would include general sociodemographic information, personal habits, anthropometric measurements, pregnancy, menstrual pattern and history, use of oral contraceptives, history of adolescence acne, history of acne in relatives, relevant comorbidities, acne pattern identification, and stress level.

Several methodological limitations within this study warrant further discussion. First, only young adults will be studied, and the sample size was decided in accordance with the size of the metabolite kit with expert opinions in metabolomics, molecular biology, dermatology, and statistics and not a power analysis. Second, diet tracking will not be performed. Third, this study has a cross-sectional design; because of the nature of this study design, interpretations of the results will be limited.

Despite these limitations, this study could be helpful in providing new diagnostic human biomarkers in acne and correlation between human biomarkers and patterns of acne. The findings of this trial may have important implications for the new approach of personal individualized therapy by identifying and differentiating the treatment methods of acne according to the biological and metabolic biomarkers based on human blood samples and patterns of acne.

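### The article promises diagnostic biomarkers, but its Methods aim is association and the only healthy-versus-acne analysis it names is a t test of means, which does not measure discrimination

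*Protocol article*

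**What the plan says.** The diagnostic aim appears in three places in the protocol article.

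- Abstract: "The purpose of this study is to investigate diagnostic human biomarkers in acne by comparing the biological and metabolic biomarkers". Its closing sentence again promises evidence on diagnostic markers.
- Section 1, Introduction: "The objective of this research is to determine the diagnostic specific human biomarkers in acne by comparing the molecular biological and metabolomics biomarkers".
- Section 3, Discussion: the study "could be helpful in providing new diagnostic human biomarkers in acne".

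The Methods put the aim differently. Section 2.1 sets out to "discover novel specific biomarkers associated with the pathogenesis of acne", to compare markers by severity, and to correlate them with symptoms and lifestyle. Section 2.7 repeats these aims and calls the study preliminary and exploratory.

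Section 2.8 follows the Methods wording. An independent t "test will be performed for the comparison of specific biomarkers associated with the pathogenesis of acne", and the groups compared are "between the healthy subjects and participants with acne vulgaris". The one-way ANOVA is confined to the three acne severity groups, and the Pearson correlations relate markers to symptoms, diet, stress, sleep and menstrual pattern. Section 2.5.4 adds unnamed statistical techniques for metabolic changes and the pathway network. The article mentions no AUC, sensitivity, specificity, cut-off or classification model, and no criterion for calling a marker diagnostic.

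**The concern.** Whether a marker's mean differs between groups and whether the marker tells a patient from a healthy person are different questions. A t test addresses the first. With enough participants, a difference too small to classify individuals usefully still reaches significance.

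The Abstract and Introduction say that diagnostic markers will be found by comparing the two groups, and the named comparison is one of means. Followed as written, the plan yields evidence of association and no estimate of discrimination. What is at stake is the headline conclusion: the diagnostic claim would rest on an analysis that does not address it. The limitations listed in the Discussion (age range, basis of the sample size, no diet tracking, cross-sectional design) do not mention this gap.

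**Working it through.** **Inputs.** 40 healthy subjects and 60 patients with acne (section 2.7); independent t test and a 95% confidence level (section 2.8); severity quotas of 20, 20 and 20 (section 2.3.1.1). Assumptions: two-sided 0.05, since sidedness is not stated, and normal data with equal variances for converting a difference into an AUC.

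**The plan's own figure.** The article gives no effect size, SD, power or interval width, so the total of 100 cannot be re-derived. Its parts agree: 20 + 20 = 40, 30 + 30 = 60, and 3 × 20 = 60.

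**Step 1: where significance starts.**
- Standard error in SD units: √(1/40 + 1/60) = 0.204.
- Critical t on 98 df: 1.984.
- Smallest significant observed difference: 1.984 × 0.204 = 0.405 SD.

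**Step 2: what that means for discrimination.**
- AUC = Φ(d/√2) = Φ(0.405/1.414) = 0.61.
- Sensitivity and specificity at the cut-off that makes them equal: Φ(d/2) = Φ(0.2025) = 0.58.

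**Step 3: chance of p < 0.05 by true difference (noncentral t).**

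| True difference (SD) | AUC | Sensitivity = specificity | Chance of p < 0.05 |
|---|---|---|---|
| 0 | 0.50 | 50% | 5% |
| 0.2 | 0.56 | 54% | 16% |
| 0.4 | 0.61 | 58% | 49% |
| 0.578 | 0.66 | 61% | 80% |

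**Step 4: distance to stronger discrimination.** An AUC of 0.80 needs d = √2 × 0.842 = 1.19 and an AUC of 0.90 needs d = 1.81. These are 1.19/0.405 = 2.9 and 1.81/0.405 = 4.5 times the difference that reaches significance.

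**Step 5: would a stricter significance level close the gap?** The number of markers is not given. Replacing 0.05 by 0.05/m in Step 1, for an assumed m of 20, 100 or 500, moves the threshold to 0.63, 0.74 or 0.83 SD, that is an AUC of 0.67, 0.70 or 0.72. Stricter testing raises the bar but still does not report discrimination.

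**Step 6: can these data give a useful AUC?** With the Hanley-McNeil standard error at 60 versus 40:

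| AUC | 95% CI |
|---|---|
| 0.61 | 0.50 to 0.72 |
| 0.70 | 0.60 to 0.80 |
| 0.80 | 0.72 to 0.88 |
| 0.90 | 0.84 to 0.96 |

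For 20 mild cases against 40 controls precision is lower. The null standard error is √(61/(12 × 20 × 40)) = 0.080, against √(101/(12 × 40 × 60)) = 0.059 for the pooled comparison.

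**The case against.** The strongest reply is that the Methods agree with one another. Sections 2.1, 2.7 and 2.8 concern discovery and association, and a comparison of means suits that. The study calls itself preliminary and exploratory, the Discussion accepts limits on interpretation and says only that the work could help, and screening by group difference before diagnostic validation is an accepted sequence. All of this stands. It makes the matter a conflict between headline and Methods, not a wrong test for the aim in section 2.1. It does not remove the conflict, because the Abstract and Introduction still give the purpose as diagnostic.

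A second reply is that discrimination analyses may sit in a fuller protocol or analysis plan, or among the unnamed techniques of section 2.5.4. That is possible, so the t test should be called the only *named* healthy-versus-acne analysis, not the only one. But section 2.5.4 points those techniques at metabolic changes and pathways in the metabolomic data, and does not cover the cytokines, zinc or skin measurements.

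A reader might go further and infer either of the following, which the article does not support:

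- **Markers with almost no discriminating ability will be declared diagnostic.** No section makes p < 0.05 the criterion for that label. An AUC of 0.61 is weak but not nil, and it describes the significance threshold, not a typical marker.
- **The plan reports over-optimistic performance because it does not resample, or because the severity quota shapes the pooled result.** The article plans no performance estimate, so there is none to be biased. Both matter only once an AUC is added, and belong with the remedy.

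**Conclusion.** The point holds as a mismatch between the diagnostic purpose in the Abstract, Introduction and Discussion and the association aim and mean comparison in sections 2.1 and 2.8. A significant t test at 40 versus 60 is compatible with an observed AUC as low as about 0.61, and the study has 80% power for a marker whose true AUC is about 0.66. Significance alone therefore cannot carry a diagnostic conclusion.

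The figures rest on a two-sided 0.05 level and equal-variance normality. Skewed cytokine values, or a wider spread in an acne group built from three severity bands, would change the exact AUCs but not the reasoning. The problem is recoverable: recruitment, sampling and assays are unaffected.

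**What to change.** Choose one of two routes and make all sections agree.

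1. **Keep the diagnostic aim.** Add to section 2.8 an AUC with 95% CI for candidate markers, for healthy subjects against all acne and against mild acne (KAGS 1–2). The second is needed because the 20/20/20 quota, not the severity mix of any target population, shapes the pooled value. Do any marker selection or panel building inside cross-validation and report the cross-validated AUC. State the aim in section 2.1 to match.
2. **Keep the association aim.** Replace the diagnostic wording in the Abstract, Introduction and Discussion with association with acne, in line with section 2.1.

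If a fuller plan already contains a discrimination analysis, a sentence in section 2.8 saying so, with section 2.1 aligned, would suffice.

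Route 1 costs some extra analysis of data already being collected. Its results will probably look less favourable than p-values do, and the mild-acne estimates will be imprecise. Route 2 costs only wording and a more modest headline.

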## Methods and analysis

2

### Aim of the study

2.1

The objective of this study is to discover novel specific biomarkers associated with the pathogenesis of acne by analyzing metabolomics/molecular biomarkers and skin biophysical parameters between healthy individuals and patients with acne, to compare the differences in these biomarkers according to the severity of acne, and to explore the correlation between such biomarkers and various factors, such as acne symptoms, dietary habit, stress level, sleep pattern, and menstrual pattern.

### Design and registration

2.2

This cross-sectional study will be conducted at Kyung Hee University Korean Medicine Hospital from May 2017 to December 2017. Patients with acne and healthy volunteers will be recruited at the same time (Fig. 1). This trial was registered in the Clinical Research Information Service (CRIS), Republic of Korea: KCT0002212. The flow chart of this study is shown in Fig. 1. A completed Standard Protocol Items: Recommendations for Interventional Trials (SPIRIT) Checklist for the trial is available (see Additional file 1).

**Figure 1 F1:**
[figure not shown]
Flow of the study.

### Participants and eligibility

2.3

#### Inclusion criteria

2.3.1

##### Participation of the population with acne vulgaris

2.3.1.1

Participants who will meet the following criteria will be included:1.Age of 19 to 35 years.2.Body mass index (BMI) of 18.5 to 23 kg/m^2^.3.Acne vulgaris [20 individuals with Korean Acne Grading System (KAGS) Gr 1 or 2; 20 individuals with KAGS Gr 3 or 4; and 20 individuals with over KAGS Gr 5).4.Voluntary participation in this clinical trial.

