### Recruitment

2.4

Through advertisements, 60 patients with acne vulgaris and 40 healthy participants will be recruited at Kyung Hee University Korean Medicine Hospital. Advertisements will be posted on the notice boards of the hospital and local community centers. Consent will be obtained by the investigators with the principle of informed consent, which confirms the participants’ voluntarism. The participants will sign the consent form that would include the information on the use of their human-derived biomaterials, that is, blood sample.

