#### Exploring biomarker with metabolomic profiling

2.5.4

This study will apply MS-based metabolomic profiling studies for the detection and identification of potential metabolic biomarkers for acne in the participants’ serum. The liquid chromatography-mass spectrometry system will consist of a Thermo Scientific Vanquish ultra-high-performance liquid chromatography (UHPLC) system (Thermo Fisher Scientific, Sunnyvale, CA) with a triple ToF 5600+ mass spectrometer system (Triple ToF MS) (SCIEX, Foster City, CA) for untargeted metabolite analysis. The UHPLC system with a QTRAP 3200TM (hybrid triple quadrupole/linear ion trap) mass spectrometry system (SCIEX, Foster City, CA). The analytical methods will be developed and optimized for targeted and untargeted analyses of metabolites, such as steroidal hormones (dehydroepiandrosterone, androstenedione, testosterone, dihydrotestosterone, estrone, and estradiol), fatty acids (oleic acid; cis, elaidic acid; trans, palmitic acid; saturated), and endogenous small metabolites closely related to energy metabolism and lipid/steroid biosynthesis. Statistical techniques will be used to investigate the particular metabolic changes and entire network of the metabolic pathway profile.

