### Sample size

2.7

The current study is a preliminary cross-sectional trial with the aims of discovering novel specific biomarkers in acne by investigating metabolomics/molecular biomarkers between healthy individuals and patients with acne, comparing the differences in these biomarkers according to the severity of acne, and exploring the correlation between the biomarkers and acne symptoms. In other words, this study is, to the best of our knowledge, the first of its kind and not intended to validate affirmatively the effects of certain interventions on acne, but rather to compare the biomarkers of patients with acne with those of healthy individuals. If the aims of the pilot study do not include any hypothesis tests, the power level of a test procedure is not a valid consideration for sample size.^[20]^ Moreover, in the metabolomics study design, a sample size of 3 to 5 per group may give useful preliminary data that can be used to design more elaborate and/or targeted metabolomics studies and the number of sample size for a metabolomics experiment depends on the biological variability associated with the system being studied compared with the analytical variability of the analytical system.^[21]^ Therefore, in this exploratory study, the number of patients to be included will be set to 40 healthy subjects (20 men and 20 women) and 60 patients with acne (30 men and 30 women) which enables the assessment of the difference in metabolomics/molecular biomarkers between healthy individuals and patients with acne including a respective 95% confidence interval, with sufficient precision according to the size of the metabolite kit with expert opinions in metabolomics, molecular biology, dermatology, and statistics.

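### The severity ANOVA has no sex term and the sex and severity quotas are not crossed, so sex-steroid differences by acne grade could be partly confounded by sex

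*Protocol article*

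**What the plan says.** All references are to the protocol article.

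- **Aim of the study:** one stated aim is "to compare the differences in these biomarkers according to the severity of acne".
- **Participation of the population with acne vulgaris:** after 20 patients with grade 1 or 2, the quota continues "20 individuals with KAGS Gr 3 or 4; and 20 individuals with over KAGS Gr 5". No sex quota is attached to any stratum.
- **Sample size:** the totals are "40 healthy subjects (20 men and 20 women) and 60 patients with acne (30 men and 30 women". Sex is set for each main group, not for each severity stratum.
- **Recruitment:** only totals are given: "60 patients with acne vulgaris and 40 healthy participants will be recruited at Kyung Hee University Korean Medicine Hospital".
- **Exploring biomarker with metabolomic profiling:** the targets include "steroidal hormones (dehydroepiandrosterone, androstenedione, testosterone, dihydrotestosterone, estrone, and estradiol".
- **Statistical methods:** "One-way analysis of variance will be performed for the comparison of the differences in these biomarkers among 3 groups", namely mild, moderate and severe. No sex factor, covariate or within-sex analysis is named. On the level of confidence: "Statistical analyses will be conducted with a 95% confidence interval using the SPSS 21.0".
- **Questionnaire:** sex is recorded for every participant.

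**The concern.** The sex quotas make the healthy and acne groups both half men and half women, so that contrast is balanced on sex by design. The contrast across severity strata has no such protection. Any set of three counts of men that adds to 30, with none above 20, satisfies both quotas. That runs from 10/10/10 to 0/10/20.

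A one-way ANOVA has severity as its only factor. If the mix of men and women shifts with grade, a marker whose level differs by sex will have stratum means that shift too, even when it is unrelated to severity within either sex. In a study meant to find candidate markers, a sex difference could then be reported as a severity marker. If the mix does not shift, the sex difference stays in the residual variance and makes true severity differences harder to see.

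**Working it through.** **1. The plan's own figures.** By severity 20 + 20 + 20 = 60; by sex 30 + 30 = 60; with controls 60 + 40 = 100. The totals agree. There is no power calculation to reproduce: the Discussion says the size rests on "expert opinions in metabolomics, molecular biology, dermatology, and statistics and not a power analysis".

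**2. Inputs.** From the article: three strata of 20, 30 men and 30 women, one-way ANOVA, and a 95% level, read as two-sided 0.05. Assumed, because the article gives neither: the male-female difference, D within-sex SDs, taken as 1, 2 and 3; and the number of men in the mild, moderate and severe strata. The marker is taken as normal with the same SD in both sexes, the same D in every stratum, and no severity effect.

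**3. Why the split matters.** Let p be the proportion of men in a stratum.

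- Spurious severe-minus-mild difference = (men in severe − men in mild)/20 × D. At 6/10/14 this is 8/20 × D = 0.4D; at 5/10/15 it is 10/20 × D = 0.5D.
- Expected between-stratum mean square = 1 + D² × 20 × Σ(p − 0.5)²/2.
- Expected within-stratum mean square = 1 + D² × 20 × Σp(1 − p)/57.

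Sex adds to both. The test is inflated only when it adds more to the first. With D = 2 (D² = 4):

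| Men per stratum | Between | Within | Ratio |
|---|---|---|---|
| 10/10/10 | 1 + 4 × 0 = 1.00 | 1 + 4 × 20 × 0.75/57 = 2.05 | 0.49 |
| 8/10/12 | 1 + 4 × 20 × 0.02/2 = 1.80 | 1 + 4 × 20 × 0.73/57 = 2.02 | 0.89 |
| 7/10/13 | 1 + 4 × 20 × 0.045/2 = 2.80 | 1 + 4 × 20 × 0.705/57 = 1.99 | 1.41 |
| 6/10/14 | 1 + 4 × 20 × 0.08/2 = 4.20 | 1 + 4 × 20 × 0.67/57 = 1.94 | 2.16 |
| 5/10/15 | 1 + 4 × 20 × 0.125/2 = 6.00 | 1 + 4 × 20 × 0.625/57 = 1.88 | 3.20 |

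A ratio near 1 corresponds to a test near its nominal level.

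**4. False-positive rate by simulation** (20,000 or more data sets per cell, no severity effect):

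| Men per stratum | D = 1 | D = 2 | D = 3 | Sex in the model |
|---|---|---|---|---|
| 10/10/10 | 2% | 0.2% | near 0 | about 5% |
| 8/10/12 | 4% | 3% | 1% | about 5% |
| 7/10/13 | 7% | 8% | 7% | about 5% |
| 6/10/14 | 12% | 22% | 31% | about 5% |
| 5/10/15 | 18% | 45% | 70% | about 5% |

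At the permitted extreme, 0/10/20, the unadjusted rate is 76% at D = 1 and essentially 100% at D = 2.

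**5. How often imbalance arises by chance.** If sex is unrelated to grade, the numbers of men follow a multivariate hypergeometric distribution. The gap between the highest and lowest stratum is at least 4 men with probability 50%, at least 6 with 19%, at least 8 (as in 6/10/14) with 4.8%, and at least 10 (as in 5/10/15) with 0.7%. Averaged over such random splits, the unadjusted ANOVA rejects about 5% of the time for D from 0.5 to 3.

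**6. Power under perfect balance.** At 10/10/10 with D = 2 and assumed severity means of 0, 0.4 and 0.8 SD, the unadjusted ANOVA has 20% power. With sex in the model it has 59%.

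**The case against.** **The article condenses a longer document.** A full protocol, version 1.2, is mentioned under Ethics and dissemination, and it or an analysis plan may cross the quotas or adjust for sex. The stated totals are compatible with 10 men and 10 women per stratum. This stands as a caution. But the point does not rest on silence alone: the article sets the sex quota at group level and names a test that has severity as its only factor.

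**Confounding is allowed, not forced.** This stands. The article states no association between sex and grade. Small imbalance does no harm to the error rate, and random imbalance does none on average. The large rates need splits that are uncommon unless sex and grade are related among recruits. Nothing in the described design or analysis guards against such a relation, and recruitment is by open advertisement.

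**The study is exploratory and unpowered.** True, and the article says that interpretation will be limited. That lowers the stakes of one false lead. It does not remove the bias, and sex is not among the limitations listed. The loss of power also matters more in a small exploratory study.

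**Crossed quotas may be hard to fill.** Six cells of 10 at one centre, under the BMI, smoking, alcohol and medication criteria, could be slow. This stands, and it is why the model term should come first and the quota second.

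**Conclusion.** The concern holds as a conditional risk. If sex is associated with KAGS grade among recruits, the planned severity comparison of sex steroids could be partly confounded by sex. The size runs from no inflation at 8/10/12, through 7% to 8% at 7/10/13, to 12% to 31% at 6/10/14 and 18% to 70% at 5/10/15, for D from 1 to 3. D, the split, normality and an equal sex difference in every stratum are assumptions. The loss of power does not depend on imbalance; it is present even at 10/10/10.

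A reader might infer more than this:

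- *That the severity comparison is a comparison of men with women.* Among the splits examined, that is literal for mild against severe only at 0/10/20 (or its mirror image); the others give partial confounding.
- *That the quotas by themselves bias the result.* They do not; a link between sex and grade is needed.
- *That cytokines, zinc, ROS or the skin measures are equally exposed.* The article does not say which of these depend on sex, so the point is confined to the sex steroids.
- *That age also belongs in the model.* Nothing examined here makes a case for it.

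**What to change.** **Main change, in Statistical methods:** include sex as a second factor alongside severity in the ANOVA, or analyse the sex steroids separately in men and women. In the simulations the sex factor holds the error rate at about 5% at every split tried, and at 10/10/10 it recovers the lost power. Sex is already collected, so the cost is one model term and one degree of freedom. The two-factor model assumes the same sex difference in every stratum. If that is doubtful for a given steroid, the within-sex analysis avoids the assumption, at the price of smaller groups.

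**Secondary change, in the acne inclusion criteria and Sample size:** where recruitment allows, aim for 10 men and 10 women in each severity stratum. This gives 3 × 10 = 30 men and 3 × 10 = 30 women, so the same 60 patients. It also avoids a split such as 0/10/20, where an adjusted model must compare mild with severe by way of the moderate stratum. The downside is slower filling of the last places, so it is better worded as a target than as a strict limit. It does not replace the sex term, because the unadjusted test stays conservative under perfect balance.
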